## 2. **OBJECTIVES**

### **Primary objective:**

To address the extent to which (satellite-) predicted and empirically validated mosquito abundance and mapped transport/mobility connectedness among Khwaeng do associate with DENV and CHIKV exposure as measured by sero-positivity. Coupled with a detailed geographic information system (GIS) of Bangkok, including fine scale meteorological data, will subsequently enable fine scale agent-based simulation models to test *in silico* the efficacy of implementing vector control in a variety of locations.

### **Secondary objective:**

To assess knowledge, attitude, and practice (KAP) about mosquito-borne disease, control measures, and vaccine acceptance among parents

## 3. **METHODOLOGY**

### **3.1. Type of research**

This study divides into 3 parts

1. A cross-sectional school-based sero-prevalence study among children aged 10-15 years. Sero-conversion to dengue virus and chikungunya exposure will be measured by Dengue IgG Rapid Diagnostic kit and Chikungunya IgM/IgG Rapid Diagnostic kit, respectively (SD Bioline).
2. A cross-sectional questionnaire study. The questionnaire about KAP about mosquito-borne diseases among their parents who enrolled in sero-prevalence study
3. A prospective observational study of mosquito sampling study in schools and in the homes of 10% of the recruited children using sticky traps

### **3.2. Evaluation criteria**

#### **Principle evaluation criteria:**

Epidemiological read-out – sero-prevalence

To assess the association of centrality with exposure to DENV and CHIKV, we will perform a sero-prevalence study using Rapid Diagnostic kits on children 10-15 years spread across 8-12 schools in Bangkok.

#### **Secondary evaluation criteria:**

Entomological read-out. Adult mosquito numbers caught on Gravid Aedes Traps (sticky paper) weekly throughout the year in the schools and during the summer months in a sample of children's homes.

Answers to a questionnaire about knowledge, attitude, and practice about mosquito-borne disease and control measures among parents

## 4. **STUDY POPULATION AND SOURCE OF RECRUITMENT**

#### 4.1. Inclusion criteria

1. Aged 10-15 years old from schools characterised by the environmental and centrality typology.
2. Signed informed consent.

#### 4.2. Exclusion criteria

1. Suffering from any concurrent infection or with any physical or mental disability.
2. Refusal to participate.

#### 4.3. Source of recruitment

Children of ages 10-15 years old from 8-12 schools will be invited to participate. The schools will be chosen from a list (below) based on their environmental and centrality typology.

| id_sch     | name                                                                              | type | nb_stu | class         |
|------------|-----------------------------------------------------------------------------------|------|--------|---------------|
| 3110023402 | โรงเรียนรัตนจินนุทิศ                                                              | BMA  | 420    | central-_env- |
| 3110015008 | โรงเรียนสุสันทองประดิษฐ์อนุสรณ์                                                   | BMA  | 152    | central-_env- |
| 10032003   | โรงเรียนสุวรรณพลับพลาพิทยาคม                                                      | OBEC | 671    | central-_env- |
| 3110010609 | โรงเรียนวัดธรรมมาภิรตาราม                                                         | BMA  | 133    | central-_env- |
| 3110012104 | โรงเรียนวัดนวลจันทร์                                                              | BMA  | 205    | central-_env- |
| 3110013706 | โรงเรียนคลองกลั่นต้น                                                              | BMA  | 173    | central-_env- |
| 10032029   | โรงเรียนแจรงฟอนวิทยา                                                              | OBEC | 411    | central-_env- |
| 10032012   | โรงเรียนนพรัตนพาราม                                                               | OBEC | 1200   | central-_env- |
| 3110014705 | โรงเรียนอานวยกนกศิโรตธิน                                                          | BMA  | 200    | central+_env+ |
| 3110013001 | โรงเรียนวัดราชสีห์ธาราม                                                           | BMA  | 110    | central+_env+ |
| 10032013   | โรงเรียนชีโนรสวิทยลัย                                                             | OBEC | 2079   | central+_env+ |
| 10032030   | โรงเรียนวัดบวรมงคล                                                                | OBEC | 400    | central+_env+ |
| 3110022710 | โรงเรียนวัดมะลิ                                                                   | BMA  | 176    | central+_env+ |
| 3110012003 | โรงเรียนเทพวิทยา                                                                  | BMA  | 217    | central+_env+ |
| 3110024503 | โรงเรียนสุเทพาภิวนดอน                                                             | BMA  | 106    | central+_env+ |
| 3110012914 | โรงเรียนวัดรัชฎาธิฐาน                                                             | BMA  | 135    | central+_env+ |
| 3110020303 | โรงเรียนวัดปทุมวนาราม ในพระบรมราชูปถัมภ์สมเด็จพระเทพรัตนราชสุดาฯ สยามบรมราชกุมารี | BMA  | 291    | central+_env- |
| 10010003   | โรงเรียนพระตำหนักสวนกุหลาบ                                                        | OBEC | 287    | central+_env- |
| 3110011202 | โรงเรียนวัดราชสิงขร                                                               | BMA  | 444    | central+_env- |
| 10012012   | โรงเรียนเบญจมราชลัย ในพระราชูปถัมภ์                                               | OBEC | 1881   | central+_env- |
| 3110011304 | โรงเรียนวัดธรรมมงคล (หลวงพ่อยี่งค9อุปถัมภ์R)                                      | BMA  | 140    | central+_env- |
| 3110011102 | โรงเรียนวัดยานนาวา                                                                | BMA  | 110    | central+_env- |
| 10012030   | โรงเรียนวัดสุทธิวราราม                                                            | OBEC | 2899   | central+_env- |
| 3110011904 | โรงเรียนวัดศรีบุญเรือง                                                            | BMA  | 180    | central+_env- |
| 3110014508 | โรงเรียนสวัสดิ์วิทยา                                                              | BMA  | 178    | central+_env+ |
| 10012009   | โรงเรียนวัดบวรนิวาส                                                               | OBEC | 245    | central+_env+ |
| 10012001   | โรงเรียนสตรีวิทยา                                                                 | OBEC | 2917   | central+_env+ |
| 3110011002 | โรงเรียนวัดคลองลม                                                                 | BMA  | 192    | central+_env+ |
| 10012015   | โรงเรียนวัดสังเวช                                                                 | OBEC | 170    | central+_env+ |
| 3110011903 | โรงเรียนวัดเทพศิลา                                                                | BMA  | 392    | central+_env+ |
| 10022005   | โรงเรียนเทพศิลา                                                                   | OBEC | 2115   | central+_env+ |
| 10012025   | โรงเรียนไตรมิตรวิทยาลัย                                                           | OBEC | 919    | central+_env+ |
| 10012010   | โรงเรียนวัดราชบพิธ                                                                | OBEC | 1789   | central+_env+ |
| 3110010904 | โรงเรียนวัดทัศนารุณสุนทราราม                                                      | BMA  | 107    | central+_env+ |

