### **5.1. General organisation of the study**

#### **A. Sero-prevalence**

A one-time cross-sectional sero-prevalence study to measure IgG seropositivity will be performed in each of the selected schools in pupils aged 10-15 years old. The total number of participants in the research project is 1000. Collected from 2-3 schools in each of the four area types.

After consent to allow child participation, the pediatrician will use a rapid diagnostic lateral flow blood test to measure the immunity against dengue and chikungunya from the children. The blood sampling will be drawn from the fingertips for two drops (1 drop per test) at the child school. The result will be reported within the same day of the test. Parents will be required to answer the Dengue and Chikungunya questionnaires.

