#### ***For sero-conversion study (specific data collection):***

For each participating child, the age, gender, history of infection/ dengue vaccination, school name and address, house address and RDT test results for both dengue and Chikungunya will be written on the Case Report Form (CRF) immediately following the test. Information on age, sex and history of infection/ dengue vaccination will be obtained. We will also collect the school and place of residence coordinates (longitude & latitude), which will be subsequently classified in one of the four typologies Central+/Environmental+, Central+/Environmental-, Central-/Environment+, Central-/Environment aggregated to the scale of the grids as shown in Figures 1 & 2 and the coordinates information then erased.

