## 9. STATISTICAL CONSIDERATIONS

Sample size:

Based on the preliminary data showing a difference in prevalence rates according to school centrality and environmental typology (approximately 26% vs 15%), we estimate a necessary sample size of ~210 children for each of the four typologies (Central+/Environmental+, Central+/Environmental-, Central-/Environmental+, Central-/Environmental-).

Sample size was calculated as follows [17]

$$n = (Z_{\alpha/2} + Z_{\beta})^2 \cdot [p_0(1 - p_0) + p_1(1 - p_1)] (p_0 - p_1)^2$$

Where n is the required sample size per treatment arm,  $Z_{\alpha}$  and  $Z_{\beta}$  are constants set by convention according to the accepted  $\alpha$  error and whether a one-sided or two-sided effect,  $p_0$  is the proportion sero-positive in area type 0 (ie Central + or Environment +), and  $p_1$  the proportion areas type 2 (Central – or Environment –).

Assuming a  $p < 0.05$  as acceptable and a study with 90% power, the following constant values are:  $Z_{\alpha/2} = 1.96$  and  $Z_{\beta} = 0.84$ .

Because our preliminary data indicated variation within school centrality and environmental typology, (coefficient of variation ranging from 0.6-1), we used the following formula to estimate the number of different sites for each typology.

$$\text{Site number per typology} = 1 + (Z_{\alpha/2} + Z_{\beta})^2 \cdot [p_0(1 - p_0)/n + p_1(1 - p_1)/n + k^2(p_0^2 + p_1^2)] (p_0 - p_1)^2$$

Where k is the coefficient of variation and n the number of individuals as calculated above. Using  $n=210$  and  $k=0.6$  to 1, we would need at least two and optimally three schools per environmental typology with 80-100 children per school.

Sero-positivity (as defined by the manufacturers instructions) will be analysed by logistic regression with age, sex and centrality (high vs. low) and environmental typology (Open vs Dense) as explanatory variables using R. School mosquito densities will also be included as an explanatory variable. In the subset of individuals collecting mosquitoes in the homes will be taken into account in a separate analysis. Mosquito densities will also be analysed with respect to the environmental typology and meteorological parameters.

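### As printed, the school list in section 4.3 has no low-centrality, Env+ school, so one of the four planned typology cells cannot be filled by selecting on the listed class

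*Protocol*

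**What the plan says.** Section 4.3 states the selection rule, "The schools will be chosen from a list (below) based on their environmental and centrality typology", and prints a table of schools with a class for each.

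Section 5.1.A fixes the number of schools: "Collected from 2-3 schools in each of the four area types". Section 9 fixes the number of children and names the cells: "we estimate a necessary sample size of ~210 children for each of the four typologies (Central+/Environmental+, Central+/Environmental-, Central-/Environmental+, Central-/Environmental" (the last label also carries a minus sign). The Summary (items 5 and 16) and section 5 repeat the four-type structure.

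The Rationale (Summary, item 4) gives a conditional hypothesis: better-connected districts have higher exposure, to a degree that depends on how suitable the environment is for mosquitoes.

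For analysis, section 7.1 says that school and home coordinates will be "classified in one of the four typologies Central+/Environmental+, Central+/Environmental-, Central-/Environment+, Central-/Environment". Section 7.2 assigns that conversion to the mapping team and has the result linked back to the serology data.

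**The concern.** The list that must supply four kinds of school shows only three. A team that follows section 4.3 literally has no school to choose for the Central-/Env+ cell, and any school placed there would contradict its listed class. The mismatch bears on the main question, because asking whether centrality acts differently in the two environments requires low- and high-centrality schools in both. It is also an error that surfaces late. Schools are chosen and children tested first, and the typology derived from coordinates is attached afterwards, when an empty cell is no longer cheap to fill.

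**Working it through.** **Step 1. Count the class column in section 4.3, in printed order.**

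| Block | Rows | Label | Schools |
|---|---|---|---|
| 1 | 1-8 | `central-_env-` | 8 |
| 2 | 9-16 | `central+_env+` | 8 |
| 3 | 17-24 | `central+_env-` | 8 |
| 4 | 25-34 | `central+_env+` | 10 |

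Total 8 + 8 + 8 + 10 = 34. By class: C-/E- 8, C+/E- 8, C+/E+ 8 + 10 = 18, C-/E+ 0.

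**Step 2. Compare with what the design needs.** Four cells of 2-3 schools give 8-12 schools, and four cells of 210 give 840 children. With one cell empty, three cells give 6-9 schools and 3 × 210 = 630 children.

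**Step 3. See what a relabelling would do.** If block 2 is really C-/E+, the counts for C-/E-, C-/E+, C+/E-, C+/E+ become 8, 8, 8, 10. If block 4 is, they become 8, 10, 8, 8. Either way every cell could supply 2-3 schools. The identifiers favour block 2: its two OBEC schools have ids beginning 10032, as do all three OBEC schools in block 1, while the OBEC ids in blocks 3 and 4 begin 1001 or 10022. That is suggestive only.

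**Step 4. Reproduce the planned cell size.** Section 9 uses p0 = 0.26, p1 = 0.15, Z(α/2) = 1.96 and Zβ = 0.84. Reading the formula as divided by the squared difference:

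n = (1.96 + 0.84)² × [0.26 × 0.74 + 0.15 × 0.85] / 0.11² = 7.84 × 0.3199 / 0.0121 = 207.3

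This agrees with the stated ~210. (Zβ = 0.84 corresponds to 80% power, not the 90% in the text. At 1.28 the same formula gives 277.5. That is a separate matter.)

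**Step 5. Find which contrasts survive an empty C-/E+ cell.** Three cells remain: C-/E-, C+/E- and C+/E+. A model with main effects for centrality and environment has three cell-level parameters, so it fits these cells exactly. The centrality effect is then C+/E- vs C-/E-, and the environment effect is C+/E+ vs C+/E-. The interaction, and the environment contrast within low centrality, have no data.

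**Step 6. Power for the environment-adjusted centrality contrast.** Inputs are 26% vs 15%, two-sided 0.05 and no clustering, with mean proportion 0.205:

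z = [0.11 × √n − 1.96 × √(2 × 0.205 × 0.795)] / √0.3199 = [0.11 × √n − 1.119] / 0.5656

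- Three cells, 210 vs 210: z = (1.594 − 1.119) / 0.5656 = 0.84, power about 80%.
- Full design, 420 vs 420: z = (2.254 − 1.119) / 0.5656 = 2.01, power about 98%.

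If the overall target of 1000 children were kept and spread over three cells (about 333 each), z = (2.007 − 1.119) / 0.5656 = 1.57, power about 94%. Extra children in three cells still give no information on the interaction.

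**The case against.** **It is probably only a label error.** The four-block layout fits four intended classes, and the identifiers point to block 2. A reader might infer that Bangkok, or the team's list, has no low-centrality Env+ schools and that the 2x2 design is impossible. The documents do not support that: on the likelier reading, suitable schools are already listed under the wrong sign. What stands is that the protocol does not say so, and the printed column is what selection is to follow.

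**Analysis does not rely on this column.** A reader might also infer that low-centrality schools would be analysed as high-centrality, diluting the contrast. The protocol does not support this either. Sections 7.1 and 7.2 classify schools and homes from coordinates, and nothing makes the class column the analysis variable. That protects the analysis label, but not the choice of schools, which comes first.

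**The model in section 9 names no interaction.** This is correct, and both main effects remain estimable from three cells under that model. It would therefore be wrong to say that the centrality effect is lost. The loss is in precision and in the ability to examine the conditional hypothesis in the Rationale, which the four-cell sampling was evidently built to serve.

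**The sign may have been misread.** In the text version of the protocol some Thai school names are garbled, so an error in one character cannot be ruled out. It is less likely when eight consecutive rows carry the same label and the eight rows just above show `central-` correctly. The source table should still be looked at first.

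**Conclusion.** The point holds as an inconsistency between the sampling frame and the design. The list as printed has 0 of 34 schools in a cell that needs 2-3 schools and about 210 children, and no other part of the protocol repairs this.

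If schools are selected by the printed class, the dependence of the centrality effect on environment cannot be tested. The adjusted centrality contrast falls from 420 vs 420 to 210 vs 210 children, about 98% to 80% power. These powers assume the protocol's 26% vs 15% and ignore clustering. With the between-site variation that section 9 reports (coefficient 0.6-1), both would be lower, so they show the relative loss rather than the power to expect.

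That one block is mislabelled, and that it is block 2, is probable but not stated anywhere. If so, the defect is a wrong column entry. It still has to be corrected before schools are chosen.

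**What to change.** Before any school is selected:

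1. Check the class of all 34 schools against the source list and the existing centrality and environment maps, starting with the two `central+_env+` blocks.
2. Correct the class column. If neither block proves to be low-centrality, add schools that truly are Central-/Env+.
3. Confirm, and state in section 4.3, that each of the four cells has at least 2-3 eligible schools.

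The planned classification from coordinates in sections 7.1 and 7.2 can stay as it is. The cost is a check of 34 labels and a corrected table, with no change to sample size, procedures or analysis. Only if schools have to be added would there be further work in approaching them.

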## **5. PRACTICALITIES OF THE RESEARCH STUDY**

The main objectives of this study are to study the sero-prevalence of previous dengue and Chikungunya infection in 4 types of areas categorised by their centrality and degree of vegetation using rapid diagnostic IgG test kits. A second aim is to measure the mosquito abundance in schools and homes categorised by their area type. A final aim is to assess knowledge, attitudes, and practices regarding preventing Dengue fever and Chikungunya.

### **5.1. General organisation of the study**

#### **A. Sero-prevalence**

A one-time cross-sectional sero-prevalence study to measure IgG seropositivity will be performed in each of the selected schools in pupils aged 10-15 years old. The total number of participants in the research project is 1000. Collected from 2-3 schools in each of the four area types.

After consent to allow child participation, the pediatrician will use a rapid diagnostic lateral flow blood test to measure the immunity against dengue and chikungunya from the children. The blood sampling will be drawn from the fingertips for two drops (1 drop per test) at the child school. The result will be reported within the same day of the test. Parents will be required to answer the Dengue and Chikungunya questionnaires.

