#### **C. Questionnaire**

A questionnaire about knowledge, attitude and practice about dengue infection, chikungunya infection, prevention, and control measure will be administered to the parents/care givers of the participating children (1000).

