### **5.3. Benefits to the individual and the community.**

The major benefit of the study is to generate first insight into the relationship between place of school and residence (defined by centrality and environmental typology) and risk of exposure to DENV and CHIKV. The study will also generate sero-prevalence data, which can then guide the local public health authorities for any potential implementation of the Takeda QDENGAR® (Dengue Tetravalent Vaccine [Live, Attenuated]) under evaluation for authorisation in Thailand. Knowledge of sero-positivity to the dengue virus will also be of direct benefit to the individual, especially with regard to the above-mentioned vaccine. Moreover, data from KAP about mosquito-borne diseases, control measures, and vaccine acceptance can contribute to the public health prevention campaigns concerning mosquito-borne diseases.

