## 8. STUDY CALENDAR

Estimated start date of enrollment: 01/06/2024

Enrollment period: 6 months

Duration of subject's participation:

- 4 months for mosquito sampling study
- 1 day for seroprevalence study and questionnaire

Total estimated study duration: 1 year

Data analysis: 6 months

Data storage period: 2 years after the last publication before archiving the data base. Data will be kept at the Chulalongkorn University, 2 years after the last publication of the results estimated at 4 years after enrolment initiation and then archived. No individual data will be stored at Institut Pasteur.

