### **12. DISSEMINATION OF THE RESULTS**

#### **12.1. Dissemination of the results to the participants**

Information concerning the results of this study will be communicated during a session at each of the schools to which the participating children and parents will be invited.

Individual communication to the patient of their results is planned as part of this study as the result from the rapid diagnostic test is instantaneous (a matter of minutes) and the child will still be present when the result is known.

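### The protocol does not require the parent questionnaire or the infection and vaccination history to be completed before the child's test result is disclosed, so vaccine-acceptance answers and recalled history can be influenced by that result

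*Protocol*

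**What the plan says.** On the order of events, Protocol section 5.1 A (Sero-prevalence) goes from consent to the finger-prick test at school, and then: "The result will be reported within the same day of the test. Parents will be required to answer the Dengue and Chikungunya questionnaires". Section 8 gives the length of participation as "1 day for seroprevalence study and questionnaire", and item 14 of the protocol summary says the same. Section 5.1 C (Questionnaire) names the respondents and the topics but gives no timing.

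On disclosure, section 12.1 says that the test takes minutes and that "the child will still be present when the result is known". The table in section 7.2 lists guardian contact data and gives the return of individual results as one reason for holding them.

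On the outcome, section 2 makes parental knowledge, attitude and practice, including vaccine acceptance, the secondary objective. Section 9 compares willingness to be vaccinated by analysis of variance and models potential vaccine uptake with generalized linear models.

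On the link between the two, section 5.3 states: "Knowledge of sero-positivity to the dengue virus will also be of direct benefit to the individual, especially with regard to the above-mentioned vaccine". The background in section 1 adds that dengue vaccines are controversial because of possible greater severity in people not previously infected.

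On history, section 7.1 lists infection and dengue vaccination history among the child's items which, with the "RDT test results for both dengue and Chikungunya will be written on the Case Report Form (CRF) immediately following the test".

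**The concern.** The protocol itself treats the dengue result as information that bears on a vaccination decision. A parent who has just heard the result is therefore not in the same position as one who has not. If some or all parents answer after disclosure, the study measures willingness in people who have been told their child's serostatus and reports it as the attitude of the parent population. Any factor related to serostatus could then appear related to willingness partly because of what parents were told.

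The history item has a similar weakness by a different route. It goes on the form together with the result once the test is done, so whoever supplies or records it may already know whether the test was positive.

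This cannot be left to the analysis. If the order is neither fixed nor recorded, no later model can reconstruct it, and section 7.2 has the paper forms destroyed after double entry. Adding serostatus to the willingness model would not help, because it cannot separate a real association from the effect of having been told.

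**Working it through.** The point concerns procedure, and the protocol has no figure of its own to reproduce for it. The check sets the sections side by side and then sizes the mechanism under stated assumptions.

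**Order**

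1. In section 5.1 A the only ordering word is the one that places the test after consent. The sentences on the result and on the questionnaire are adjacent, with nothing saying which comes first.
2. Section 5.1 C gives no timing. Section 8 and summary item 14 give one day with no order inside it.
3. Section 12.1 has the result known in minutes, with the child present. So the result can be out before a same-day questionnaire is answered.
4. No section says that the questionnaire comes first, that the result is held back until it is handed in, or that the order is noted.
5. For history, section 7.1 does state a time for writing the items down: straight after the test, alongside the result. Its next sentence says that history will be obtained, but gives neither a time nor a respondent.

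The described procedure therefore permits disclosure first, for both items, and contains no safeguard.

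**Size (illustration only)**

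Inputs from the protocol: planning seropositivity of 26% and 15% (section 9), and pilot dengue seropositivity of 37.2% at ages 10 to 15 (section 1). Assumed, because the documents give nothing: a shift d in willingness of 5, 10 or 20 points in one serostatus group caused by hearing the result, and a share f of parents who hear it before answering. Let s be seropositivity.

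- Shift in overall willingness if only parents of positive children move: f × s × d. With f = 1 this runs from 0.15 × 5 = 0.75 points to 0.372 × 20 = 7.4 points.
- Shift if only parents of negative children move: f × (1 − s) × d. With f = 1 this runs from (1 − 0.372) × 5 = 3.1 points to (1 − 0.15) × 20 = 17 points.
- Error in a comparison of willingness between positive and negative children: f × d, so 5 to 20 points at f = 1.

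All three fall in proportion to f; if half the parents hear first, each is halved.

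For scale, with 1000 parents and willingness assumed at 50%, the 95% half-width for the overall proportion is 1.96 × √(0.25/1000) = 3.1 points, ignoring clustering by school. Most of the assumed range for parents of negative children exceeds that, and unlike sampling error it does not shrink with more respondents.

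**The case against.** The strongest reply is that the protocol never says the questionnaire follows the result. That is right. A reader might infer from section 5.1 A that disclosure is scheduled first, but this rests on sentence order alone. What stands is that the order is left open.

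Nor do the documents show that parents know the result before answering. Section 12.1 describes the child at school, and whether parents attend is not stated. Contamination is a possibility wherever the parent hears first, not an established fact for all 1000.

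A reader might go on to infer a false difference in willingness between the four area types, since seropositivity is expected to differ between them. The documents do not support that as a harm to a planned result. Summary item 16 stratifies seroprevalence and mosquito abundance by typology but not the questionnaire, and section 9 names neither area type nor serostatus as a factor for willingness. It would also be small: (0.26 − 0.15) × d gives 1.1 to 3.3 points even for d of 10 to 30. Against that, the 95% half-width for two groups of 1000/4 = 250 at 50% willingness is 1.96 × √(2 × 0.25/250) = 8.8 points.

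Extending the point to knowledge scores and reported practice also goes beyond the text, because sections 1 and 5.3 tie serostatus only to the vaccine. Infection history is not a documented item of the parent questionnaire and is not in the section 9 seropositivity model; section 7.2 gives it a descriptive purpose. That limits the damage from prompted recall but does not remove it.

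Finally, how late questionnaires are handled in the analysis may be settled in a statistical analysis plan. The order of steps on the day is study conduct and belongs in the protocol.

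**Conclusion.** The point holds as a missing safeguard. Vaccine acceptance is a secondary objective and a modelled outcome, the protocol says that serostatus bears on the vaccine, and the described procedure lets the result reach the parent before the questions are answered. The history item carries a separate risk of prompted recall, which rests on section 7.1 alone.

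The documents give no size for either effect, and the figures above depend wholly on the assumed shift and on how many parents hear first. Test positivity is determined before anyone is told, so the primary endpoint and the sample size are untouched. This is worth correcting before enrolment because it cannot be repaired afterwards, but it is confined to secondary and descriptive data.

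**What to change.** In sections 5.1 A, 5.1 C and 7.1, state that the parent questionnaire is completed and handed in, and that infection and vaccination history is recorded, before the test result is disclosed. The consent contact is a natural moment, since section 10.1 already requires signed parental consent before a child is recruited. Add one field showing whether each questionnaire was completed before or after disclosure, and carry it into the database so that it survives destruction of the paper forms.

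Same-day return of the result can stay as it is. The cost is a reordering of steps and one extra field. The drawback is that parents who do not attend the school must return the form before test day, which may delay some children or lose some questionnaires; the field identifies any that arrive late.
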